
**Fig. 3 Fig3:**
[figure not shown]
Overview of EEG pre-processing pipeline. FIR, finite impulse response; IIR, infinite impulse response; ICA, independent component analysis; AMICA, adaptive mixture ICA; ICs, independent components; Hz, Hertz

Via LORETA-KEY software (v20210701, freely available at http://www.uzh.ch/keyinst/loreta.htm), ASCII text files will be used as input to compute cross-spectral matrices for each participant for seven frequency bands (infraslow 0.01–0.1 Hz; slow 0.2–1.5 Hz; delta 2–3.5 Hz; theta 4–7.5 Hz; alpha 8–12 Hz; beta 12.5–30 Hz; gamma 30.5–44 Hz) utilizing fast Fourier transform (FFT). To allow for 2 complete cycles of the lowest frequency of interest (i.e. 0.01 Hz) and to obtain smooth power spectral density, EEGs will be segmented into 200-s epochs with Hanning (Hann) tapered windows applied. The cross-spectral matrices will then be averaged for each subject and used as input to exact LORETA (eLORETA) to compute whole-brain current source density (CSD; A/m^2^) without assuming a pre-defined number of active sources [242, 243]. Using the MNI-152 (Montreal Neurological Institute, Canada) template, eLORETA produces an inverse solution space consisting of 6239 cortical grey matter voxels at 5 mm resolution and has been shown to produce exact, zero-error localizations even in the presence of measurement and structured biological noise. eLORETA performs voxel-by-voxel between-condition comparisons of the CSD distribution. Statistical non-parametric mapping (SnPM) will be performed for each contrast using built-in voxel-wise randomization test (5000 permutations) to calculate the empirical probability distribution for the max-statistic (e.g. the maximum of a *t* or an *F* statistic) under the null hypothesis while correcting for multiple testing (i.e. for the collection of tests performed for all electrodes and/or voxels, and for all time samples and/or discrete frequencies). For each contrast, the voxel-level, two-tailed max-statistic was used as input to LORETA-KEY software to identify and visualize differences/changes in log-CSD for each of the seven frequency bands. Furthermore, for each condition, log-CSDs were averaged across all voxels within a 10-mm radius of the centre of mass MNI coordinates derived from previous literature [244] of the targeted ROIs (Fig. 4). This output was exported to Excel (version 2112) and analysed in R (version 4.0.5 [245];) to identify differences/changes in log-CSD between contrasts for each ROI in each frequency band. Next, functional connectivity (FC; i.e. lag-CON [242]) between the targeted ROIs was calculated for each group at each time point in LORETA-Key. Output was then exported to Excel and analysed in R to identify differences/changes between contrasts in each frequency band. Finally, as effective connectivity (EC) reflects directed functional connectivity, significant ROI pairs identified from FC analyses were selected for EC (i.e. Granger causality [246]) analyses. As with FC, EC was calculated in LORETA-Key, exported to Excel, and analysed in R.

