Although traditional frontline therapies (i.e. pharmacotherapy and psychotherapy) are effective for many, they offer numerous shortcomings including high failure rates [92–98], lack of access [22, 99–102], and marked adverse side-effects [52, 99, 100, 103–105]. Closed-loop brain training of electrophysiological (EEG) signals, also known as EEG-neurofeedback (EEG-NFB), is a non-invasive therapy aimed at modulating brain function by teaching individuals, via associative learning (e.g. operant conditioning), to self-regulate their brain function via auditory, visual, and/or tactile feedback [106]. Intriguingly, EEG-NFB’s impact on the brain may intensify following the cessation of therapy putatively due to treatment-induced neuroplasticity; however, a general lack of extended follow-up and failure to assess for the emergence of delayed treatment effects is common in the literature [107]. That said, sceptics assert that comparable clinical improvements in both experimental and control groups in randomized, double-blind, sham-controlled trials suggest that EEG-NFB's efficacy rests entirely on ‘non-specific’ psychosocial factors (i.e. expectations, motivation, demand characteristics, context) [108–119]. However, proponents contend that evidence of differential EEG-learning (i.e. greater change in the targeted electrophysiological variable(s) and/or region(s)-of-interest (ROIs) in the genuine versus sham groups), considered by many to be essential for a valid evaluation of EEG-NFB’s specificity [120–126], was noticeably absent in the trials presented as evidence for wholly non-specific effects [127, 128]. That said, assessments of differential EEG-learning are complicated by a lack of standardized criteria for the determination of learning (or a lack thereof) [129]. In any case, EEG-NFB has shown promising clinical effects in a wide various of conditions [130–135] including IDs [102, 136–155]. Further, clinicians have reported success in ID populations using sensor-space EEG-NFB targeting eISFs (ISF-NFB) [156–158]. Advanced source-localization (i.e. standardized LORETA, sLORETA [62]) combined with ISF-NFB is a novel introduction to the field that has been shown by our research group in a feasibility trial on obese females to improve sleep and wellbeing with minimal side-effects [159, 160].

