Continuous, real-time auditory feedback will be used for reinforcement and produced within 30 ms of the subject’s eISFs (0.0–0.1 Hz) within the pre-defined ROIs (i.e. dACC and/or PCC; Fig. 1) surpassing the threshold(s). These ROIs were selected because, as outlined in the introduction, they are considered key cortical nodes within the core RSNs which are consistently found to be disrupted in ID populations. sLORETA permits the selection of any cortical region for feedback of the current density using voxels selected based on Montreal Neurological Institute (MNI) coordinates [211]. For a complete list of targeted voxels for this trial, see Additional files 1 and 2.

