### Measurements

#### Primary outcomes: HADS, fb-EEG

The central importance of PROs in clinical trials has been emphasized by both international health regulatory agencies and patients [216, 217], therefore, the *primary* outcome of interest will be the HADS [218, 219]. Additionally, the importance targeted EEG-learning assessments in NFB trials has been emphasized by researchers [120–126], therefore activity (i.e. amplitude of the oscillations) and connectivity (i.e. coordinated amplitude and/or phase of the oscillations) changes within and between the targeted ROIs will also be of primary interest. Primary outcome measures will be collected at baseline, post 6 sessions, post 12 sessions, and 1-month follow-up.

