### Statistical considerations

#### Objective 1

Between-group (sham vs. ISF1 and ISF2) comparisons post-6 sessions will be performed for the PROs and neurophysiological measures. For this analysis, we will use LORETA-Key software and a Bayesian model with random effects to allow for baseline differences and non-specific temporal effects between participants. A sensitivity analysis will be carried out to compare this approach with an ANCOVA that includes a linear baseline adjustment.

#### Objective 2

Regression methods will be used to explore the relationship between changes in the primary PRO subscales (i.e. HADS-A, HADS-D) and targeted ROI activity and connectivity for all participants post 6 sessions.

#### Objective 3

Within-group (ISF1 and ISF2) comparisons between post-6 sessions and post-12 sessions will be performed for all outcome measures. The same model will be applied as in Objective 1 where random effects will now allow for post-6 session differences between participants.

#### Objective 4

Within-group (ISF1 and ISF2) comparisons between post-12 sessions and 1-month follow-up will be performed for all outcome measures. This will use the same model as Objective 1 where random effects will now allow for post 12-session differences between participants.

#### Objective 5

Regression analysis from Objective 2 will be extended to post 12-session and 1-month follow-up for the ISF1 and ISF2 groups.

Analyses were performed using LORETA-KEY software, R, JAGS [299] and Stan [300] with analysis-specific details described below. For all endpoints, responses were modelled assuming a normal distribution (e.g. with group-specific means and variances or via regression). When normality assumptions were not met, appropriate transformations were performed. Additionally, potential endpoint covariates were examined (e.g. age); however, none exhibited correlations that were strong enough to warrant inclusion for denoising purposes in the models. For the Bayesian analysis, JAGS or Stan was linked to R using the rjags or rstanarm library with estimates based on 3 chains of 25,000 iterations with a burn-in/warm-up = 10,000 iterations. Vague priors were used throughout.

Bayes’ theorem postulates that the probability of an event A given event B is proportional to the probability of event B given event A multiplied by the prior probability of event A:$$P\left(A|B\right)\propto P\left(B|A\right)\ast P(A)$$

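### The primary EEG outcome names no frequency band and is examined in seven bands, though only the infraslow band is trained, so chance differences in untrained bands can be reported as primary results

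*Protocol article*

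**What the plan says.** - **Status of the outcome.** Under Primary outcomes: HADS, fb-EEG, activity and connectivity "changes within and between the targeted ROIs will also be of primary interest". No band is named there.
- **Bands and measures.** The Full-band EEG section uses LORETA-KEY to "compute cross-spectral matrices for each participant for seven frequency bands", one of them infraslow (0.01–0.1 Hz). Log-CSD is averaged within each targeted region (PCC, dACC) and taken into R "to identify differences/changes in log-CSD between contrasts for each ROI in each frequency band". PCC–dACC lagged connectivity is then "analysed in R to identify differences/changes between contrasts in each frequency band".
- **Contrasts.** Statistical considerations, Objective 1, compares sham with ISF1 and with ISF2 after six sessions.
- **What is trained.** Intervention descriptions ties the reward to "eISFs (0.0–0.1 Hz) within the pre-defined ROIs". Under Randomization, ISF1 trains the PCC only; ISF2 trains the PCC up and the dACC down.
- **Why the outcome is primary.** Background and rationale describes differential EEG-learning as "greater change in the targeted electrophysiological variable(s) and/or region(s)-of-interest (ROIs) in the genuine versus sham groups" and reports that many regard it as essential for judging specificity. It adds that standardized criteria for learning are lacking.
- **Error control.** The whole-brain voxel-wise maps have a max-statistic permutation correction. None is stated for the region-level and connectivity analyses in R. "Vague priors were used throughout". Results are graded by pd (95, 97, 99, 99.9%) and by percentage in ROPE; none of these is made the criterion for a claim.

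**The concern.** The EEG outcome is meant to show whether genuine training changed the trained signal more than sham did. That needs a defined signal. As written, any of seven bands, in either region or in their connectivity, for either active arm, supplies a result with primary status, and most of these were never trained. The article itself notes that criteria for EEG-learning are unsettled, then sets none. Objective 2 relates HADS changes to targeted region activity and connectivity, again without a band. At stake is the interpretability of the trial's target-engagement measure: a chance difference in, say, the beta band would stand in the report beside, and with the same status as, a difference in the signal the participants were rewarded for.

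**Working it through.** The article states no alpha, power or family-wise error rate, so there is no planned figure to reproduce.

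**1. Count the contrasts.** Measures: 2 region activities (PCC, dACC) + 1 connectivity pair = 3. Bands: 7. Active arms against sham: 2.

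3 × 7 × 2 = 42.

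Of these, 3 × 6 × 2 = 36 lie in the six untrained bands. The other 6 are infraslow. Two of those 6 concern the dACC in ISF1 (its activity, and its connectivity with the PCC), and ISF1 does not train the dACC. That leaves 4 contrasts on trained regions in the trained band.

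**2. Translate the labels.** Under vague priors and a normal model, pd above a cut-off c corresponds approximately to a two-sided p below 2(1 − c): pd >95% to 0.10, >97% to 0.06, >99% to 0.02, >99.9% to 0.002. This mapping is an assumption. The random effects described are between participants, so no shrinkage across bands or measures is described.

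**3. Expected chance results.** 42 × 0.10 = 4.2 contrasts with pd >95% under no effect, whatever the correlation between measures.

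**4. Chance of at least one.** If independent, 1 − (1 − a)^42. With correlation, a null simulation was used: arms of 30, 15 and 15, a shared sham arm, t-based posteriors standing in for vague priors, and equal correlation between measures. The article gives no correlations, so 0 to 0.8 was assumed.

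| Label | a | 42 contrasts, independent | 42 contrasts, simulated (correlation 0.8 to 0) |
|---|---|---|---|
| pd >95% | 0.10 | 98.8% | about 62–99% |
| pd >97% | 0.06 | 92.6% | about 45–92% |
| pd >99% | 0.02 | 57.2% | about 21–56% |
| pd >99.9% | 0.002 | 8.1% | about 3–9% |

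On the ROPE labels, with correlations from 0.7 to 0, the simulated chance of at least one is 43–75% at below 2.5% in ROPE and 22–38% at below 1%.

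**5. After restriction to the 4 trained infraslow contrasts.** If independent, 1 − 0.90^4 = 34.4% at pd >95% and 1 − 0.98^4 = 7.8% at pd >99%. Over the assumed correlations the simulated values are about 25–35% and 6–8%.

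**The case against.** **Not every contrast is a chance of EEG-learning.** If learning means change in the targeted variable, a gamma-band difference does not qualify. Training direction is also fixed. Counting only right-direction infraslow activity (PCC up in two arms, dACC down in ISF2) gives about 1 − 0.95^3 = 14% at pd >95% and 1 − 0.99^3 = 3% at pd >99%. This stands against any claim that a false EEG-learning finding is nearly certain. It does not rescue the plan. The and/or in the article's description lets a change in the targeted region count without reference to band, no direction rule is stated for the analysis, connectivity has no direction, and all seven bands fall under the primary outcome as worded.

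**The loosest label is only suggestive.** pd >95% is graded as possible existence, and the stricter labels bring much lower rates. This also stands, and it is why the result must be given as a range by label.

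**Objective 2.** A reader might infer that it will be built on whichever band stood out in Objective 1. The article does not say so. The only result-driven selection it states is that "significant ROI pairs identified from FC analyses were selected for EC".

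**Pilot scope and an unseen analysis plan.** The Sample size section limits conclusions to potential efficacy, and multiplicity detail may sit in a document not shown. Both points soften the matter. But the breadth of the primary outcome is fixed in the article itself, and a pilot needs an interpretable measure of target engagement as much as a larger trial does. The max-statistic correction is real, but as described it does not extend to the region-level and connectivity analyses in R.

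**Conclusion.** The concern holds in limited form. The primary EEG outcome spans 42 contrasts, 36 of them in bands that are not trained, with no band given priority and no multiplicity control stated for these analyses. Under no effect, about four would reach the lowest pd label. At least one would do so with a probability of about 62–99%, falling to 21–56% at pd >99% and 3–9% at pd >99.9%. These figures rest on assumed correlations, on the correspondence between pd and p under vague priors, and on the planned arm sizes.

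The documents do not support calling a false EEG-learning claim nearly certain. That level is reached only at the loosest label with weakly correlated measures, and only if untrained bands are allowed to count. What they do support is that chance differences in untrained bands could be reported as primary EEG results. This should be corrected, but it does not invalidate the trial.

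**What to change.** In Primary outcomes: HADS, fb-EEG:

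- Name the primary EEG outcome as infraslow (0.01–0.1 Hz) activity and connectivity in the regions each arm trains: PCC log-CSD in ISF1 and ISF2; dACC log-CSD and PCC–dACC connectivity in ISF2. dACC activity and connectivity keep their primary status, because dACC down-training is what distinguishes ISF2 and connectivity is part of Objective 2.
- Use the same infraslow variables as the EEG measures in Objective 2.
- Label the other six bands, and the ISF1 contrasts involving the dACC, as exploratory and not evidence of EEG-learning.
- Report the number of contrasts examined.
- State that a result reaching only pd >95% will not be read as EEG-learning, since the four contrasts still carry about 25–35% at that label against 6–8% at pd >99%.

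The cost is wording: no new data are needed and every band can still be reported. The downside is that findings in untrained bands become hypothesis-generating only. Timing also matters. Trial status expected data collection to finish by the end of 2021, the article appeared in November 2022, and parts of the statistical section are in the past tense. If the EEG data have already been analysed, the labelling must be disclosed as late.

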
**Fig. 4 Fig4:**
[figure not shown]
Regions-of-interest (ROIs) and their centre of mass coordinates. MNI, Montreal Neurological Institute; dACC, dorsal anterior cingulate cortex; PCC, posterior cingulate cortex

#### Secondary outcomes: MEDI, IDAS-II, IUS-12, RTQ-10, HRV

The Multidimensional Emotional Disorder Inventory (MEDI) [247, 248], Inventory of Depression and Anxiety Symptoms – Second Version (IDAS-II) [249, 250], Intolerance of Uncertainty Scale – Short Form (IUS-12) [251], and Repetitive Thinking Questionnaire (RTQ-10) [252–254], and heart rate variability (HRV) will be considered *secondary* outcomes of interest which are also collected at baseline, post 6 sessions, post 12 sessions, and 1-month follow-up.

##### Multidimensional emotional disorder inventory (MEDI)

The MEDI, which has been validated on both clinical [247] and non-clinical [255] populations, is a 49-item, trans-diagnostic PRO measure that employs a response scale ranging from 0 (not characteristic of me/does not apply to me) to 8 (extremely characteristic of me/applies to me very much) to assess nine ID-related symptom domains, originally proposed by Brown and Barlow [256], including (1) Neurotic Temperament (5 items), (2) Positive Temperament (5 items), (3) Depression (5 items), (4) Autonomic Arousal (5 items), (5) Somatic Anxiety (5 items), (6) Intrusive Cognition (6 items), (7) Social Concerns (5 items), (8) Traumatic Re-experiencing (5 items), and (9) Avoidance (8 items). Although validated clinical severity thresholds for the MEDI total subscale scores are still lacking, the authors of this measure have suggested that average subscale scores >4 (or <4 for positive temperament), >6 (or <2 for positive temperament), and 7–8 (or 0–1 for positive temperament) may reflect moderate, severe, and extreme severities, respectively [257].

##### Inventory of depression and anxiety symptoms – second version (IDAS-II)

The IDAS-II is a valid and reliable 99-item, trans-diagnostic PRO measure that uses a response scale ranging from 1 (not at all) to 5 (extremely) to assess 19 current (past 2 weeks) ID-related symptom domains including general depression (20 items), dysphoria (10 items), lassitude (6 items), insomnia (6 items), suicidality (6 items), appetite loss (3 items), appetite gain (3 items), well-being (8 items), ill temper (5 items), mania (5 items), euphoria (5 items), panic (8 items), social anxiety (6 items), claustrophobia (5 items), traumatic intrusions (4 items), traumatic avoidance (4 items), checking (3 items), ordering (5 items), and cleaning (7 items) [249, 250]. Notably, in contrast to the other domains, the general depression domain is a composite of all 10 items from the dysphoria domain, as well as 2 items each from the suicidality, lassitude, insomnia, appetite loss and well-being domains. Recently, severity (mild, moderate, severe) thresholds have been introduced for 12 of the subscales including general depression, dysphoria, lassitude, insomnia, suicidality, appetite loss, appetite gain, well-being, ill-temper, panic, social anxiety, and traumatic intrusions [258].

##### Intolerance of uncertainty scale – Short form (IUS-12)

The IUS-12 is a valid and reliable 12-item, transdiagnostic PRO measure that assesses the degree to which an individual considers the possibility of a negative event occurring unacceptable, irrespective of its probability of occurrence [251, 259]. Whereas the original IUS-27 was GAD-specific, the IUS-12 has been distilled in order to measure the core intolerance of uncertainty construct [260]. The IUS-12 uses a response scale from 1 (“not at all characteristic of me”) to 5 (“entirely characteristic of me”) with total scores that can range from 12 to 60 [251]. Although some researchers have claimed that the IUS-12 is a unidimensional construct and recommend using only the IUS-12 total score [261–263], there has been considerable support for a two-factor IUS-12 structure: (1) a 7-item prospective IU scale related to action/approach-oriented strategies in order to increase certainty (e.g. seeking more information), and (2) a 5-item inhibitory IU associated with inaction/avoidance-oriented thoughts and behaviours (e.g. delayed decision-making) [251, 259, 264–271]. Intolerance of uncertainty (IU) is a common trait shared across the ID spectrum [271–274].

##### Repetitive thinking questionnaire (RTQ-10)

The RTQ-10 is a 10-item, trans-diagnostic PRO measure [253] distilled from three disorder-specific scales: 1) the MDD-associated Ruminative Responses Scale (RRS [275]), 2) the GAD-associated Penn State Worry Questionnaire (PSWQ [276]), and 3) the SOC-associated Post-Event Processing Questionnaire-Revised (PEPQ-R [277]). Participants are asked to rate the truthfulness of each statement with respect to their experience when they are “distressed or upset.” All items are rated along a 5-point scale: not at all true = 1, somewhat true = 3, or very true = 5 allowing total scores that can range from 10 (low levels of latent repetitive negative thinking) to 50 (extremely high levels of repetitive negative thinking). Repetitive negative thinking (i.e. rumination and worry) is a characteristic feature of IDs [278–280].

##### Heart rate variability (HRV)

Heart rate variability (HRV) is the phenomenon of cyclical beat-to-beat changes in the interbeat interval (i.e. RR interval), the dynamics of which can give insight into cardiac autonomic function [281]. ANS function is purportedly modulated by the core-ICNs and one of the most robust ANS disturbances found in IDs is cardiac dysautonomia in the form of reduced HRV [52, 96, 103, 280, 282–293]. This has significant clinical implications considering that cardiovascular disease is the leading cause of mortality in people with mental illness [52, 294, 295]. HRV is typically measured via the standard time-domain (i.e. standard deviation of normal-to-normal intervals, SDNN (ms), root mean square of successive differences between normal-to-normal intervals, RMSSD (ms)) and frequency-domain (i.e. LF-HRV = 0.04–0.15 Hz and HF-HRV = 0.15–0.4 Hz absolute power (ms^2^)) indices, however, non-linear analyses (e.g. Poincaré plot) are fast emerging as a way to characterize the complex, non-linear dynamics of cardiac-ANS interactions [296]. The raw ECG signals will be extracted in EEGLAB and saved as EDF (.edf) files. Using MATLAB 2021a and modifications to the open-source code for HRVTool version 1.07 (https://github.com/MarcusVollmer/HRV) [297], ECG time-series will be band-pass IIR filtered (10–35 Hz, 4^th^ order Butterworth) to remove signal drift and line noise, undergo automated annotation of R-peaks, and be interpolated using the shape-preserving piecewise cubic Hermite interpolating polynomial (Pchip) method to correct for artefacts (e.g. ectopic or missing beats). Pchip interpolation was chosen because appears to perform best across the spectrum of HRV metrics as it preserves the linear trend as well as the non-linear contributions in the R-R timeseries [298]. Using the HRVTool graphical user interface (GUI), Poincaré plots will also be examined to look for evidence of regularities (e.g. ‘comet’ shape) with those showing marked irregularities suggestive of cardiac arrhythmias (e.g. ‘fan’ shape) excluded from further analyses. Next, the first 10 s of ECG traces will be truncated to allow for signal stabilization followed by manual inspection/correction of the succeeding 5 min (i.e. 10–310 s) to ensure proper annotation of R-peaks generated from normal sinus rhythm with traces requiring >5% R-R interval interpolation excluded from further analyses. Finally, using the GUI’s R-R tachogram (time-series and spectrum), consecutive 60-s epochs (i.e. 1–5 min) from spontaneous breathing ECGs will be examined with those suggesting mean respiration rates outside of 0.15–0.4 Hz (i.e. 9–24 breaths per min) excluded from further analyses. Indices for both spontaneous and paced breathing conditions will be reported.
